## Methods

### Study Design

This randomized clinical trial used a full 2³ (2×2×2) factorial design based on the multiphase optimization strategy (MOST) framework to test and compare three intervention approaches: (1) a family-strengthening intervention, (2) trauma-focused child mental health services, and (3) asset-based economic empowerment via Child Development Accounts (CDAs).

Multicomponent interventions are often tested as “bundles,” making it difficult to disentangle the contributions of individual components. The MOST is a systematic method that allows for the testing of the independent effects of different intervention components to identify their most optimal combination [15]. While multiarm randomized controlled trials are costly, often limited in arms, and require larger sample sizes, the MOST uses a factorial design. By comparing combinations of experimental conditions, the study can have a greater number of conditions without a substantial increase in sample size. This is advantageous in LMICs, where it is essential to implement only the most efficacious aspects of a program. The MOST consists of three phases: (1) preparation, (2) optimization, and (3) evaluation of the optimized intervention in a randomized controlled trial [16]. This study falls within the optimization phase.

This study includes 3 factors—the intervention approaches—each with 2 levels (delivered/“on” or not delivered/“off”). This is a full 2×2×2 factorial design, meaning that the study has 8 different experimental conditions or groups (2^3^=8) [17]. Child-parent dyads (n=439) were randomly assigned to 1 of 8 groups (about 54 dyads per group), which determined the combination of interventions they received. Given this design, half of the sample (n≈220) received each intervention (eg, families assigned to groups 1‐4 received the family-strengthening intervention and were compared with families from groups 5‐8; Table 1).

**Table 1. T1:** Experimental conditions^a^.

Group	Usual care	Experimental interventions		
	Standard deinstitutionalization program	Family strengthening	Trauma-focused mental health services	Economic empowerment
1	On	On	On	On
2	On	On	On	Off
3	On	On	Off	On
4	On	On	Off	Off
5	On	Off	On	On
6	On	Off	On	Off
7	On	Off	Off	On
8	On	Off	Off	Off

a Child-parent dyads (n=439) are randomly assigned to 1 of 8 experimental conditions (~54 dyads per group), determining how many and which intervention components participants receive.

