### Participant Timeline

Families were recruited in 3 major cities (Baku, Sumgayit, and Ganja). Trained local research assistants (RAs) distributed recruitment materials to recruiters who invited families to join the study. Local research staff provided additional information to interested candidates and obtained informed consent. To minimize potential pressure on children and parents, consent was obtained by a research staff member rather than by representatives of local authorities.

After obtaining informed consent, RAs conducted a screening interview to determine participant eligibility. Potential participants were offered a choice of either US $1 or equivalent nonmonetary compensation (eg, toys, football) for completing the interview. To promote retention, participants provided their addresses, email addresses, and telephone numbers at baseline, along with contact information for at least 3 other individuals who could assist in reaching them. After completing the baseline survey, families were informed of their randomized intervention assignment.

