### Randomization

The principal investigator (PI) conducted the randomization prior to the start of recruitment. Eight computer-generated random numbers (ranging from 0 to 100) were assigned to the 8 intervention conditions and ranked from lowest to highest to determine the allocation sequence within each city. The first 5 families recruited in a city were assigned to the first intervention condition in the sequence. After 5 families had been assigned to each intervention condition, allocation resumed at the beginning of the sequence. To reduce predictability, the random numbers were generated from a range of 0 to 100 rather than 1 to 8. A secure, web-based, password-protected database was used to maintain the randomization record.

Data collectors were masked to participants’ intervention group assignments. To foster fidelity to the intervention manuals and maintain the integrity of each separate intervention, facilitators delivered only 1 type of intervention and were not trained in the specific content of the other intervention strategy. Due to the nature of the recruitment procedures, participants could not be blinded to the existence of other intervention conditions.

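### Families were allocated in runs of five in a fixed, repeating order, and the wider random-number range does not reduce predictability as the article says

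*Protocol article*

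**What the plan says.** The Randomization section of the protocol article describes the whole scheme. On timing: "The principal investigator (PI) conducted the randomization prior to the start of recruitment". Eight computer-generated numbers, one per condition, were "ranked from lowest to highest to determine the allocation sequence within each city". Families then entered in runs: "The first 5 families recruited in a city were assigned to the first intervention condition in the sequence". Once all eight conditions had been filled: "After 5 families had been assigned to each intervention condition, allocation resumed at the beginning of the sequence". No new draw is described at that point. The stated protection is: "To reduce predictability, the random numbers were generated from a range of 0 to 100 rather than 1 to 8".

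The same section says that the allocation record was kept in a password-protected database and that data collectors were masked. Participant Timeline adds when assignments became known: "After completing the baseline survey, families were informed of their randomized intervention assignment".

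The covariates in Analytical Strategy (Aim 1) are given by example: child's age and gender, and caregiver characteristics. The limitations in the Discussion do not mention the allocation method.

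**The concern.** The sentence about the number range claims a property that the design does not have. Ranking eight numbers yields an order of eight conditions, whatever range the numbers came from. Prediction is possible because each condition is given to five consecutive families and because the order then repeats unchanged. Neither feature depends on the range.

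Two things are at stake. First, entry order decides the condition. A person who could foresee the next condition and had any say in which family came next could influence who received what. Second, even without any steering, the conditions appear in the same calendar order in every cycle within a city. Drift in season, referral source or staff can therefore line up with condition, and the covariates named would not pick this up.

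**Working it through.** The article gives no figure for predictability, so there is none to reproduce. What follows is a direct count.

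Inputs:
- Conditions: 8 (Study Design: "the study has 8 different experimental conditions or groups").
- Run length: 5 families (Randomization). One cycle is 8 × 5 = 40 families per city.
- Cities: 3 (Participant Timeline).
- Families: 305, taking each of the 305 caregivers in Results as one family. This is an assumption.
- Families per city: not given. I use 102, 102 and 101 for illustration; all possible splits of 305 were also checked.

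1. **Number range.** If there are no ties, each condition has a 1/8 chance of coming first, whether the numbers come from 0–100 or are a random permutation of 1–8. The range changes only the chance of a tie:
   - integers 0–100: 1 − (101 × 100 × … × 94)/101⁸ = 24.8%
   - integers 1–8 drawn with repeats: 1 − 8!/8⁸ = 99.8%

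   The wider range makes ranking workable. It leaves the runs of five and the repeated order as they are.

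2. **Assignments that can be determined.** Take an observer who knows the rule and sees earlier assignments in the city. In the first 40 families, only the first family of each run is uncertain, and the eighth condition follows by elimination. From family 41 on, nothing is uncertain. With n families in a city, the uncertain number is min(7, ⌈n/5⌉).
   - Three cities: 3 × 7 = 21 uncertain, 21/305 = 6.9%
   - Determinable: 305 − 21 = 284, 284/305 = 93.1%

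3. **Sensitivity to the assumptions.**
   - Without elimination of the eighth condition: 24 uncertain, 281/305 = 92.1%.
   - Over all city splits: 93.1% to 97.0%, so 93.1% is the minimum. The upper end arises when two cities have at most five families each: 1 + 1 + 7 = 9 uncertain, 296/305.
   - One order shared by all cities and an observer who sees all of them: 7 uncertain, 298/305 = 97.7%.

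4. **A less informed observer.** Someone who does not know the rule and guesses the same condition as the last family in the city misses only at the start of each run. With 102, 102 and 101 families there are 21 runs per city, 63 in all; three of these starts are blind guesses at 1/8. Expected correct: (305 − 63 + 3/8)/305 = 79.5%.

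5. **Timing of disclosure.** Families learn their condition only after baseline. If enrolment overlapped, an earlier assignment in the same run might not yet have been known. That matters mainly in the first cycle. With the even split, 62 + 62 + 61 = 185 of 305 families (60.7%) entered after it, when the full order had been used once and a count of families was enough.

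6. **Calendar order.** There are 305/(3 × 40) = 2.5 cycles per city on average. In each, the first condition in the order starts 7 × 5 = 35 families before the eighth.

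**The case against.** Several points on the other side deserve weight.

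- **Safeguards exist.** The record was protected and data collectors were masked. Research assistants both screened families and administered surveys, so if their masking held, those who judged eligibility knew little. Families were told their condition only after consent, screening and baseline. This limits who could have known. It does not remove the problem: a protected list does not stop inference from assignments already disclosed, and masking is not stated for the recruiters who invited families or the staff who obtained consent.
- **Runs of five have a practical reason.** Family strengthening and financial education were delivered in groups of five families. That explains the runs but does not make the sentence about predictability true.
- **The model is not bare.** Baseline is already the reference point in the Aim 1 model, baseline covariates are included, and baseline comparability across conditions is reported. A general call for baseline adjustment would add little.
- **Drift is diluted.** Each main effect sets four conditions against four, over about 2.5 cycles per city. No size of bias can be derived from the article.

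A reader might infer more than the text supports. One such inference is that allocation was not concealed after the first cycle, or that enrolment was steered; the article does not show that anyone enrolling families knew the rule, followed the assignments or acted on them. Another is that the model leaves out city and enrolment order; the covariates are an example list in a condensed article, so one can say only that neither is named. A third is that the trial rests on exactly three random draws; the wording fits a separate draw per city or one draw used in all three.

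**Conclusion.** The point holds as a misstatement and an undisclosed weakness of the allocation scheme. The range of 0–100 does not reduce predictability. At least 284 of 305 assignments (93%) could be determined by someone who knew the rule and saw every earlier assignment in that city. This counts one caregiver as one family and uses elimination for the eighth condition; without elimination it is 92.1%. It becomes 97.7% if one order served all three cities and the observer saw all of them. These are figures for what could be known, not for what was known or used, and they do not measure bias. The alignment of condition with calendar order within each cycle follows from the scheme itself and needs no assumption about anyone's conduct. Allocation is finished, but the article says that effect analyses are still under way, so the reporting and the analysis can still be improved.

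**What to change.** 1. Delete or correct the sentence on the number range. Describe the scheme as fixed-order allocation in runs of five, predictable to anyone who knew the rule and saw earlier assignments, and add this to the limitations. State whether the order was drawn per city or once.
2. In the primary model, or in a sensitivity analysis fixed before effect estimates are examined, adjust for city and enrolment date within city, with their interactions with time. Effects for city by cycle alone are not enough: they remove differences between cycles but not drift within a cycle, where the conditions are ordered.
3. Add a randomization test that re-draws the condition order as it was actually drawn. If one order served all cities, the simple on-versus-off contrast for one component has only 8!/(4! × 4!) = 70 possible patterns, so its smallest two-sided P value is 2/70 = 0.029. That limit should be stated.
4. Where logs exist, report refusals and exclusions by the condition that was next in line.

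The cost is wording, data from enrolment records and a few degrees of freedom. Enrolment date is partly collinear with condition within a cycle, so some precision is lost. No new data collection is needed.

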### Outcome Measures

As presented in Table 2, the primary mental health outcomes include child-reported symptoms of depression (20-item Center for Epidemiological Studies Depression Scale for Children) [41], posttraumatic stress (8-item Children’s Revised Impact of Events Scale) [42], self-esteem (20-item Tennessee Self-Concept Scale-Second Edition) [43], attention-deficit/hyperactivity disorder (ADHD) symptoms (caregiver and teacher-reported 19-item ADHD Rating Scale-IV) [44], and general social-emotional functioning (caregiver and teacher-reported 25-item Strengths and Difficulties Questionnaire) [45]. Grades from school records and teacher-reported school behaviors (eg, completing homework, fights with other students) are also outcomes of interest. The Strengths and Difficulties Questionnaire has been validated in the Azerbaijani language [46]. Child mental health outcomes among families randomized to the mental health services were also assessed by a clinician-administered Health of the Nation Outcome Scales for Children and Adolescents (15 items) [47].

**Table 2. T2:** Measurement instruments^a^.

Outcomes and measurement instrument	Respondent
Outcomes (study aim 1)	
Internalizing and externalizing problems	
Center for Epidemiological Studies Depression Scale for Children	Child
Strengths and Difficulties Questionnaire	Caregiver, teacher
ADHD Rating Scale IV	Caregiver, teacher
Health of the Nation Outcome Scales Child and Adolescent Mental Health	Clinician rated
Traumatic symptoms	
8-item Children’s Revised Impact of Events Scale	Child
Cognitive and executive functioning (attention, cognitive control-response inhibition or impulsivity, working memory)	
*The Cambridge Neuropsychological Test Automated Battery*, a digital battery of nonverbal cognitive tasks to assess motor function, processing speed, working memory, executive functioning, and emotion recognition bias through the Motor Screening Task, Reaction Time, Spatial Span, Stockings of Cambridge, and Emotion Bias Task, respectively. *The Wechsler Intelligence Scale for Children* Block Design and Picture Span subtests to assess nonverbal reasoning and visuospatial working memory, respectively.	Child (Digital paradigm tasks)
Self-concept	
Tennessee Self-Concept Scale-Second Edition	Child
Social support	
Social Support Scale for Children	Child
School performance	
Academic performance (grades), school behaviors	Teacher, admin records (school)
Child-parent mediators (study aim 2)	
Child-parent relationship	
Brief Family Relationship Scale; Multidimensional Scale of Perceived Social Support	Child, caregiver
Parenting skills and practices	
Parenting Styles and Dimensions Questionnaire; Child Discipline	Caregiver, child
Parental distress	
21-item Depression Anxiety Stress Scale; Brief COPE	Caregiver
Socioeconomic deprivation, savings, and assets	
The rate of savings, asset accumulation, employment, type and stability of housing, financial security, and attitudes to saving and income-generating activities	Caregiver, admin records (bank statements)
Moderators	
Child’s sociodemographics	
Sociodemographic questionnaire (child’s age, gender, birth order)	Child, caregiver
Parent and family characteristics	
Sociodemographic questionnaire (parent’s gender, age, marital status, employment status, family size, family structure)	Caregiver
Parent	
Adverse Childhood Experiences International Questionnaire	Caregiver
Service use	
Types of services, the number of sessions attended	Admin records

a This table outlines outcomes, mediator, and moderators of interest.

Additional child-reported measures include social support (24-item Social Support Scale for Children) [48] and parental discipline (11-item Child Discipline Index) [49]. Child cognitive functioning was assessed using selected measures from the Wechsler Intelligence Scale for Children, Fifth Edition (WISC-V) [50] and the Cambridge Neuropsychological Test Automated Battery (CANTAB) [51]. WISC-V measures included Block Design, which assesses visuospatial reasoning and problem-solving abilities, and Picture Span, which evaluates visual working memory. CANTAB measures included the Emotional Bias Task, which assesses emotional processing and interpretation bias; the Motor Screening Task, which evaluates sensorimotor function and task comprehension; Reaction Time, which measures processing speed and attention; the Stockings of Cambridge, which assesses executive functioning and planning; and Spatial Span, which measures visuospatial working memory capacity.

Caregiver-reported measures include parenting style (32-item Parenting Styles and Dimensions Questionnaire, Short version) [52]; parental mental well-being symptoms, including depression, anxiety, and stress (21-item Depression Anxiety Stress Scale) [53]; parental experiences of childhood trauma (19-item Adverse Childhood Experiences International Questionnaire) [54]; family relationships (19-item Brief Family Relationship Scale) [55], coping strategies (28-item Brief COPE) [56]; and social support (12-item Multidimensional Scale of Perceived Social Support) [57]. The caregiver survey also assessed economic well-being (eg, employment status, financial security) and saving attitudes.

The baseline questionnaire collected information on sociodemographic characteristics (eg, child and caregiver age and gender), family composition (eg, caregiver marital status and household size), and the child’s institutional history (eg, age at placement and type of institution). For participants receiving the economic intervention, bank statements provided data about the monthly savings and asset accumulation rate.

### Data Collection

Children, their caregivers, and their teachers completed surveys at baseline, year-1, and year-2 follow-up. Child and caregiver data were collected through interviewer-administered surveys conducted separately in Azerbaijani by trained graduate-level psychology students serving as RAs. Assessments were conducted at local field offices using iPads and the cloud-based Qualtrics survey platform and required approximately 50 to 60 minutes to complete. Teacher surveys were completed independently. All surveys contained the same scales, except for demographic data that do not vary over time (eg, ethnicity, age). Except for nonverbal digital cognitive tasks (WISC and CANTAB), all instruments were translated into Azerbaijani and tested in a pilot feasibility study. The CANTAB battery consists of simple computer-administered nonlinguistic tasks considered highly precise and largely independent of cultural and language differences [58].

Intervention participation and utilization data (eg, attendance, session completion, and types of services received) were collected from intervention administrative records. Information about children’s academic performance (eg, grades) was collected from school records.

### Postintervention Qualitative Interviews

Semistructured interviews will be conducted with children, caregivers, and service providers (n=60) representing each intervention condition following the completion of intervention sessions and follow-up assessments. Interviews will explore participants’ experiences with the interventions, including perceived benefits, acceptability of intervention components, impacts on family relationships and child well-being, and barriers and facilitators to participation. Service providers (eg, mental health clinicians, family strengthening facilitators, and financial education coaches) will provide additional perspectives on implementation, training, organizational, and cultural factors affecting intervention delivery. Participants will be randomly selected from the 7 active intervention conditions within each city; the control condition will be excluded from qualitative sampling.

### Analytical Strategy

Descriptive statistics will characterize the sample and assess the variables’ psychometric and distributional properties (eg, potential outliers). The analysis will also include process measures for intervention implementation and cost estimation of intervention delivery, following Weinstein et al [59] and Gold’s [60] guidelines. Additional analyses will be performed in conjunction with the study aims:

Aim 1: To estimate the effects of intervention components on child mental health outcomes, differences in outcomes (eg, depression score) will be tested across 3 time points (baseline, 1 year, and 2 years), under an intent-to-treat basis, using linear mixed models. This approach accounts for the autocorrelation of observations nested within individuals over time. We will use logistic functions for binary outcomes (eg, mental health symptoms above the clinical cutoff), Poisson or negative binomial functions for count outcomes (eg, the number of aggressive behaviors), and linear functions for continuous variables (eg, self-esteem score). Statistical inference will be based on F-statistics and their associated *P* values for between-subject effects (the intervention assignment × time terms). To estimate the main effects for the 3 intervention components, we will determine if there is a difference in change across time using the baseline as the reference point (eg, 1 year vs baseline; 2 years vs baseline). We will also include 2-way interactions between components (eg, Family Strengthening by Economic Empowerment by Time interaction). Since we will use effect (–1, 1) coding rather than dummy (0, 1) coding, the power for tests of main effects and interactions will be identical for similarly sized effects. Covariates will include baseline attributes for outcome variables (eg, child’s age and gender, caregiver characteristics).Aim 2: To test which intervention component is mediated by hypothesized mediators, including (1) supportive parenting (eg, quality of child-parent relationships), (2) emotion regulation (eg, self-regulation), and (3) parental stress (eg, stress response). We will use a 2-step process [61] to test (1) a measurement model using confirmatory factor analysis that examines the relationships between the latent constructs and their indicator variables and (2) a structural model to test the hypothesized relationships between the latent mediating and outcome constructs and the intervention [62]. We will use the maximum likelihood method of parameter estimation with missing data. We will also conduct separate analyses to examine the effectiveness of intervention components in specific subgroups (eg, by gender).Aim 3: Qualitative analysis will be conducted in both Azerbaijani and English to explore barriers and facilitators to intervention participation and implementation. Bilingual investigators and 2 additional coders will independently review interview transcripts and conduct thematic analysis [63] and content analysis [64] using Dedoose [65]. Analyses will assess themes and concepts regarding participants’ and intervention facilitators’ perspectives on mental health needs, intervention engagement and acceptability, changes in family relationships and dynamics, and contextual and sociocultural factors influencing intervention delivery and outcomes.

In the data analysis, the primary outcomes include children’s mental health and socioemotional functioning. Secondary outcomes include cognitive and social processes associated with mental health, as well as functional outcomes related to academic performance and social functioning in the school setting. Specifically, primary mental health outcomes include child-reported depressive symptoms, posttraumatic stress symptoms, and self-esteem; caregiver- and teacher-reported ADHD symptoms and general socioemotional functioning such as internalizing and externalizing problems; and clinician-administered mental health outcomes among families randomized to the mental health services condition. Secondary outcomes include child cognitive functioning, assessed using WISC-V and CANTAB tasks; child-reported social support, particularly peer support; and teacher-reported grades and school behaviors. Mediating variables include caregiver-reported parenting practices, caregiver mental health, family functioning, coping strategies, social support, saving attitudes, and household economic well-being.

The main analyses focus on treatment effects at the 1-year and 2-year follow-ups, with the 1-year follow-up used to assess initial intervention effects and the 2-year follow-up used to assess the maintenance of those effects over time. Children from the same family will be accounted for using mixed-effects models, with random effects specified to adjust for the nonindependence of observations among children nested within the same family. Missing outcome data will be handled using maximum-likelihood estimation under a missing-at-random assumption, with sensitivity analyses using multiple imputation. To address the multiple testing issue, we will control the false discovery rate using the Benjamini-Hochberg procedure [66,67]. This approach was selected instead of Bonferroni correction because it limits false discoveries while avoiding the overly conservative loss of power associated with Bonferroni adjustment when multiple related hypotheses are tested.

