### Power Calculations

Power calculations were conducted using the G*Power software [18,19]. To account for the repeated-measures design, power estimates were modeled across a range of effect sizes at 2 assumed autocorrelation values (ρ). Analyses were performed for a 2-tailed test with a type 1 error rate of 0.05 and desired power of 0.80, assuming a final analyzed sample size of 360 child participants (180 participants per intervention type) after a projected 10% attrition from an initial planned sample of 400 child participants (200 participants per intervention type). The results indicate that for continuous outcomes, 80% power is achieved for effect sizes between 0.09 and 0.12. The study is sufficiently powered to detect small-to-medium effects [20] for continuous outcomes over the entire follow-up period. In the MOST design, the study is powered based on the intervention component with the smallest effect size—in this case, the family-strengthening component.

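### Component effects are set up as differences in change from baseline with no stated baseline adjustment; on the usual reading this costs precision, not validity

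*Protocol article*

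**What the plan says.** Under Analytical Strategy, Aim 1, differences in outcomes "will be tested across 3 time points (baseline, 1 year, and 2 years"), so baseline is a response in the linear mixed model. Inference rests on "between-subject effects (the intervention assignment × time terms"). For the main effects of the three components, "we will determine if there is a difference in change across time using the baseline as the reference point", with year 1 against baseline and year 2 against baseline as the examples. Two-way component interactions by time are included, with effect coding.

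On adjustment the article says only: "Covariates will include baseline attributes for outcome variables (eg, child’s age and gender, caregiver characteristics"). The baseline score of the outcome is not among the examples, and no constraint on the baseline means is described. Equally, nothing says that those means are left free.

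Under Power Calculations, "power estimates were modeled across a range of effect sizes at 2 assumed autocorrelation values". Neither value is given.

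**The concern.** A component × time model with baseline as the reference visit conventionally carries a component main effect as well. That lets the baseline means differ between levels, and the interaction term is then the difference in change scores. In a randomised comparison with baseline measured before assignment is disclosed, any baseline difference is chance. A model that uses this fact estimates the same follow-up effect with smaller variance whenever ρ is below 1.

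The trial needs this precision. The Discussion concedes limited power for smaller interactions and for subgroups, and Benjamini-Hochberg was preferred to Bonferroni to avoid losing power. With effect coding, the same proportional loss applies to the component × component × time terms.

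Chance imbalance is also plausible. Families were allocated in runs of five, so 305 caregivers (taking one per family) make about 305/5 = 61 batches over eight conditions. A change score over-corrects such an imbalance when ρ is below 1.

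**Working it through.** **Inputs.** From Power Calculations: "2-tailed test with a type 1 error rate of 0.05 and desired power of 0.80", and "assuming a final analyzed sample size of 360 child participants (180 participants per intervention type"), which gives 180 children at each level of a component. ρ is not given, so 0.1 to 0.9 is shown as an assumption. The derivation further assumes a continuous outcome with equal variance s² at each visit, complete data and no family clustering.

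**The plan's own figures.** The attrition step reproduces: 400 × 0.9 = 360. The detectable range of 0.09 to 0.12 cannot be reproduced from what is stated, because neither ρ nor the effect-size metric is named. Read as G*Power's f with three visits and N = 360, it is matched by a two-group between-subject test at ρ = 0.1 (0.094) and 0.5 (0.121). It is also matched by an eight-group × time test at ρ = 0.5 (0.093) and 0.2 (0.118). A two-level component × time test gives 0.095 at ρ = 0 and 0.067 at ρ = 0.5, so it does not reach 0.12 for any ρ ≥ 0. The range therefore does not reveal which ρ was assumed.

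**Variance per child of the contrast at one follow-up**

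- Change from baseline, free baseline means: 2s²(1 − ρ)
- Baseline-adjusted: s²(1 − ρ²)
- Ratio, adjusted to change: (1 + ρ)/2
- Precision lost by the change contrast: 1 − (1 + ρ)/2 = (1 − ρ)/2
- On the standard-error scale: 1 − √[(1 + ρ)/2]

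A generalised least squares calculation for the three-visit model confirms both variances. Free baseline means give the change-score variance, and a common baseline mean gives the adjusted one.

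**Detectable difference** in SD units, 80% power, with v the variance above divided by s²: (1.960 + 0.8416) × √v × √(2/180) = 0.2953 × √v.

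| ρ (assumed) | v, change | v, adjusted | Loss, variance scale | Loss, SE scale | Detectable, change | Detectable, adjusted |
|---|---|---|---|---|---|---|
| 0.1 | 1.80 | 0.99 | 45% | 26% | 0.396 | 0.294 |
| 0.3 | 1.40 | 0.91 | 35% | 19% | 0.349 | 0.282 |
| 0.5 | 1.00 | 0.75 | 25% | 13% | 0.295 | 0.256 |
| 0.7 | 0.60 | 0.51 | 15% | 8% | 0.229 | 0.211 |
| 0.9 | 0.20 | 0.19 | 5% | 3% | 0.132 | 0.129 |

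At ρ = 0.5, a change analysis with 80% power would have about 90% with adjustment. Put differently, 360 × 0.75 = 270 children analysed with adjustment give the precision of 360 analysed as change.

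**Other correlation patterns.** If correlation decays with time (first-order autoregressive, ρ from 0.7 to 0.3 between adjacent visits), the loss is 15% to 35% at year 1 and 26% to 46% at year 2. For the mean of both follow-ups under equal correlation it is 20% at ρ = 0.7 and 60% at ρ = 0.1.

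**The case against.** The strongest objection is that free baseline means are an inference. The quoted sentences also fit a constrained longitudinal model, which likewise has baseline as a response and component × visit terms. The covariate list is illustrative, and its wording could be stretched to include the baseline score. This stands as a limit on certainty: a reader might infer that the plan commits to unconstrained baseline means, and the text does not say so. Two things keep the point alive. A common baseline mean departs from the default and is normally stated. And adding the baseline score as a covariate while baseline is also a response would put the same measurement on both sides of the model, so that reading needs correcting too.

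A second objection is that such detail belongs in an analysis plan that is not shown. The article does, however, fix the contrast itself, and it is that stated contrast which can be improved.

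Third, the size is assumed. A reader might take a loss of 15% to 45% as a property of this trial. It holds only for ρ between 0.7 and 0.1, on the variance scale. At ρ = 0.9 the loss is 5%, or about 3% on the standard-error scale. The figures also do not carry over directly to the planned logistic and count models, to incomplete data, or to siblings (107 of 305 caregivers had more than one child enrolled).

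Fourth, adjustment is not entirely free. A common baseline mean relies on exchangeability at baseline under a fixed, repeating sequence of batches of five. In its favour, Participant Timeline says that families learned their assignment after the baseline survey. Nor are the two forms of adjustment interchangeable. The Results show baseline depression scores for 425 children and posttraumatic stress scores for 429, out of 439. With the baseline score as a covariate, children without one drop out unless it is imputed.

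Finally, this is a late change to a plan described as prespecified. That calls for open dating; it does not argue for the less precise contrast.

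**Conclusion.** The point holds as one of efficiency. As written, and on the usual reading, each component effect is a difference in change scores, whose precision is lower by (1 − ρ)/2 than that of a baseline-adjusted contrast. The direction is the same for every ρ below 1, so the recommendation does not depend on the undisclosed correlation; only the gain does, from 45% at ρ = 0.1 to 5% at ρ = 0.9.

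A reader might go further and conclude that the planned analysis is biased or its type I error inflated. The documents do not support that: under randomisation the change contrast is valid. The improvement is worth making because the baseline data are already collected and the Abstract reports the effect analyses as still ongoing.

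**What to change.** - **Continuous outcomes:** keep baseline as a response, but give it one mean common to all eight conditions, adjusting for city. Put component × visit and component × component × visit effects at years 1 and 2 only, and keep the family random effect. This retains children whose baseline score is missing.
- **Binary and count outcomes:** model years 1 and 2 as responses with the baseline value as a covariate, imputing missing baseline values.
- **Assumption:** state that the common mean relies on exchangeability at baseline under the batch-of-five allocation.
- **Timing:** date the change as made before effect results were seen, or disclose that it was not. Cover the two planned interim analyses in that statement.
- **Sensitivity analysis:** keep the change-from-baseline model.
- **Power:** give the two ρ values behind the calculation.

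The cost is a short paragraph of analysis text, a dated record of the change, and imputation of the few missing baseline scores for the non-continuous models. No new data are needed.
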